## Abstract

**Background:**

Preventable adverse drug events (pADEs) are widely known to be a health care issue for hospitalized patients. Surgical patients are especially at risk, but prevention of pADEs in this population is not demonstrated before. Ward-based pharmacy interventions seem effective in reducing pADEs in medical patients. The cost-effectiveness of these preventive efforts still needs to be assessed in a comparative study of high methodological standard and also in the surgical population. For these aims the SUREPILL (Surgery & Pharmacy in Liaison) study is initiated.

**Methods/Design:**

A multi-centre controlled trial, with randomisation at ward-level and preceding baseline assessments is designed. Patients admitted to the surgical study wards for elective surgery with an expected length of stay of more than 48 hours will be included. Patients admitted to the intervention ward, will receive ward-based pharmacy care from the clinical pharmacy team, i.e. pharmacy practitioners and hospital pharmacists. This ward-based pharmacy intervention includes medication reconciliation in consultation with the patient at admission, daily medication review with face-to-face contact with the ward doctor, and patient counselling at discharge. Patients admitted in the control ward, will receive standard pharmaceutical care.

The primary clinical outcome measure is the number of pADEs per 100 elective admissions. These pADEs will be measured by systematic patient record evaluation using a trigger tool. Patient records positive for a trigger will be evaluated on causality, severity and preventability by an independent expert panel. In addition, an economic evaluation will be performed from a societal perspective with the costs per preventable ADE as the primary economic outcome. Other outcomes of this study are: severity of pADEs, number of patients with pADEs per total number of admissions, direct (non-)medical costs and indirect non-medical costs, extra costs per prevented ADE, number and type of pharmacy interventions, length of hospital stay, complications registered in a national complication registration system for surgery, number of readmissions within three months after initial admission (follow-up), quality of life and number of non-institutionalized days during follow-up.

**Discussion:**

This study will assess the cost-effectiveness of ward-based pharmacy care on preventable adverse drug events in surgical patients from a societal perspective, using a comparative study design.

**Trial registration:**

Netherlands Trial Register (NTR): NTR2258

## Background

Incidents caused by medications are a widely recognized issue in hospitalised patients. These incidents are known as Adverse Drug Events (ADEs), usually defined as 'any injury due to the use of medication' [1]. These may occur as an unavoidable result of the pharmacological action (side effect or Adverse Drug Reaction) or by the manner in which a drug is applied (medication error or substandard care). A preventable ADE (pADE) is defined as 'any injury caused by a medication error'. These pADEs are associated with substantial mortality and morbidity rates [2]. Besides clinical consequences, preventable ADEs have a considerable impact on health care costs [3,4].

A recent systematic review shows that 15.1% of all in-hospital adverse events (AEs), is medication related (i.e. ADEs) [5]. Current estimates show a large variance in the incidence of preventable ADEs--i.e. from 0.6 - 16 per 100 admissions [4,6-14], due to variability in population and variability in the sensitivity of detection methods. Surgical patients are typically at risk due to the transfer moments of surgical patients, medication changes before and after surgical intervention and a relatively frequent use of medications associated with a high prevalence of AEs, such as analgesics, anticoagulants and antibiotics [5,9]. The incidence of pADEs in surgical patients is unclear because of the absence of large studies using a standardized and general applicable detection method to determine pADEs in the surgical population.

In order to reduce the incidence and costs of in-hospital ADEs, several computerized strategies are developed, e.g. computerized order checking, barcode medication administration or computerized physician order entry (CPOE) with clinical decision-support system [10]. However, even in highly computerized hospitals, high rates of preventable ADEs remain [12]. Among health care professionals within the hospital organization, clinical pharmacists can fulfil a vital role in improving medication safety by face-to-face interaction with physicians and patients [15-17]. Instead of fulfilling the responsibility for the appropriate, safe and cost-effective use of medication from a central pharmacy, without patient contact or direct access to information on the clinical status of the patient and without face-to-face contact with the physician or nurses, nowadays active participation of pharmacists in the ward is common practice in countries such as the UK, USA and Australia [15]. This active participation of hospital pharmacists in the clinical process--also known as 'ward-based pharmacy care'--can reduce the occurrence of ADEs effectively with 66%-78% in medical and intensive care units [16,17]. Their activities consist of close review of medication at admission, active participation in multidisciplinary rounding teams, and counselling patients at discharge [15].

Only few studies have investigated the economic impact of the contribution of pharmacists to the clinical process [18-20]. Bond et al. studied the associations between clinical pharmacy services and total cost of care in approximately 1000 general surgery hospitals in the US. Clinical pharmacy services were associated with a cost saving per hospital per year of 5-8 million USD [18].

The departments of hospital pharmacy and surgery in the Academic Medical Centre in Amsterdam, The Netherlands, initiated the SUREPILL study: Surgery & Pharmacy in Liaison. The goal of this comparative study is to evaluate whether ward-based clinical pharmacy care can reduce (preventable) adverse drug events cost-effectively in elective surgical patients. The economic impact will be assessed from a societal perspective with incremental cost-effectiveness analyses of clinical pharmacy interventions against standard care. According to a recent systematic review there still is a need for comparative studies of high methodological standard measuring the effect of clinical pharmacy interventions in general [21]. Moreover, incidence of pADEs and preventability by a ward-based pharmacy team in surgical patients with more complex use of medication is not yet evaluated.

The main purpose of the SUREPILL study is to answer the following questions: 1) Will active participation of a clinical pharmacy team in surgical wards reduce preventable ADEs? 2) Will a clinical pharmacy team be cost-effective in reducing preventable ADEs in surgical wards receiving ward-based pharmacy compared to control wards receiving standard pharmaceutical care?

## Methods/Design

### Design

To answer the research questions, a multi-centre controlled trial, with randomisation at ward-level is designed. Participating centres are the Academic Medical Centre (AMC), the Onze Lieve Vrouwe Gasthuis (OLVG) in Amsterdam and the Diakonessenhuis in Utrecht. In each centre at least two surgical wards will participate. These study wards contain mainly gastro-intestinal and vascular surgical patients.

The study design is depicted schematically in figure 1. First, baseline assessments in each hospital in the participating surgical wards will be performed. Then, in each centre, one ward will be randomly assigned (one-time randomisation) as intervention ward, receiving ward-based pharmacy care, whereas the other ward(s) will serve as control ward, receiving standard pharmaceutical care from the central hospital pharmacy (i.e. current daily practice).

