### Sample size and data analysis

The power calculation is based on the parallel comparison of the number of pADEs per 100 admissions between patients admitted at the intervention ward (with ward-based pharmacy care) and those admitted at the control ward (with standard care). We expect a mean base rate of five preventable ADEs per 100 admissions in the control group. This rate is conservatively estimated, based on the incidence of pADEs per 100 admissions in prospective observational studies in hospitalised patients (pooled mean 2.1%, range: 0.6%-16.2% [4,6-14]) and observed rates in control groups of intervention studies on the effect of clinical pharmacy on pADEs (pooled mean 11.6%, range: 11.4%-12% [16,17,26,35]). The difference in incidence rate between the observational and intervention studies can be predominantly explained by a higher sensitivity of ADE detection methods employed in the intervention studies.

In this study population, we hypothesize a relative reduction in pADEs of 60%. This hypothesis is based on the findings of two controlled studies assessing ward-based pharmacy in non-surgical wards, showing a reduction of 66% and a reduction of 78% [16,17].

With all admissions equally distributed over intervention and control wards, a sample of 964 admissions achieves 80% power at a 0.05 one-sided significance level to detect a reduction in the number of pADEs per 100 admissions from 5 to 2 or below (rate ratio <0.4), resulting from ward-based pharmacy care compared to standard care. To control for ward-specific ADEs at baseline, 480 patients equally distributed over the participating surgical wards, will be included at start. Hence, the total number of patients amounts to 1444 (480 + 964). This number of patients will be distributed over the participating centres according to their proportion of number of admitted patients in the wards.

With the total number of 1444 patients a Poisson regression of the number of pADEs with the type of treatment (intervention or control) as the main covariate of interest can be performed to detect a rate ratio below 0.4 with 80% power at a significance level of 0.05. This is performed while adjusting for other covariates like, for instance, hospital site, ward type, observation period, ADE levels at baseline, and patient age, even if these other covariates explain as much as 50% of the variance in pADE counts by type of treatment.

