## Discussion

Measuring cost-effectiveness of clinical pharmacy is complex. Criteria for such research are not standardized. Recently, several recommendations have been stated in a systematic review [21], such as comparative design including a control group, providing details of clinical pharmacy interventions, considering health benefits, considering the effect of program factors (e.g. type of ward and hospital, and level of expertise of clinical pharmacist), considering applicability in other settings, taking a societal perspective when evaluating clinical pharmacy interventions, and including sensitivity and incremental cost-effectiveness analyses. The present study design meets these criteria.

For this study we choose a parallel design with preceding baseline assessment and with randomisation at ward level to assess the incidence of pADEs at baseline in the participating study wards and to determine the impact of the ward-based pharmacy care as well as to take into account the impact of differences between the observed study wards. Furthermore, a large number of factors are suggested to increase the risk of ADEs in hospitalised patients, such as drug characteristics (e.g. route of administration), patient-specific factors (e.g. number of medications taken) [9] and organisational factors (e.g. communication) [38]. These drug characteristics, patient-specific and organisational factors influence the incidence and severity of ADEs, but it is unknown to what extent. Therefore, the ideal situation to test the impact of a pharmacy team on clinical and economic outcomes would consist of an equal distribution of all these factors in experimental and control group. Straightforward comparison of two wards, with one ward only experimental and the other ward only control patients, implies the risk of unbalanced confounders because of the differences between the wards, patients and its staffing. By adding a baseline assessment it is possible to adjust for a priori differences between wards. In this manner a clear insight of the sole impact of the ward-based pharmacy care on pADEs is obtained.

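### No restriction on ward type is described for the one-ward-per-centre draw; if each centre pairs one ward of each type, there is a 25% chance that all intervention wards share a type, an avoidable risk

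*Protocol article*

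**What the plan says.** The Design section has three centres with at least two surgical wards each. After the baseline assessments, "Then, in each centre, one ward will be randomly assigned (one-time randomisation) as intervention ward", and the remaining ward or wards serve as control. No link between the three draws and no balancing on ward type is described. On case mix the section says only: "These study wards contain mainly gastro-intestinal and vascular surgical patients". It does not say which ward holds which patients.

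The Sample size and data analysis section plans a Poisson regression "adjusting for other covariates like, for instance, hospital site, ward type, observation period", with baseline ADE levels and patient age as further examples. It states that "a sample of 964 admissions achieves 80% power at a 0.05 one-sided significance level", and it gives the baseline phase its own purpose: "To control for ward-specific ADEs at baseline, 480 patients equally distributed over the participating surgical wards, will be included at start".

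The Discussion recognises the hazard of comparing single wards: "Straightforward comparison of two wards, with one ward only experimental and the other ward only control patients, implies the risk of unbalanced confounders". Its answer is the baseline assessment.

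**The concern.** With only three draws, chance imbalance on a ward characteristic is a practical possibility. If wards within a centre differ in surgical type and the draws are unrestricted, every intervention ward may turn out to be of one type and every control ward of the other. In the intervention phase, treatment and ward type are then the same variable, and only the baseline phase can separate them. The concern named in the Discussion for a two-ward comparison would reappear at the level of the whole trial. Randomisation is done once, so no later analysis can undo such a draw. At stake are the precision of the primary comparison and its protection against time trends that differ by ward type.

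**Working it through.** **Inputs from the article (Sample size and data analysis).** One-sided 0.05; 80% power; 5 v 2 pADEs per 100 admissions (rate ratio 0.4, |log| = 0.916); 964 intervention-phase admissions, 482 per arm; 480 baseline admissions.

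**Assumptions, not in the article.** Exactly two equal wards per centre, one of each type; no ward-level variation beyond the fitted terms; no true period or type effect.

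**Step 1. The plan's own figures.**
- Two Poisson rates, unpooled difference: N = 2 × (0.05 + 0.02) × (1.645 + 0.842)² / 0.03² = 962, against 964 stated.
- Poisson-regression sample-size formula with half the patients exposed: 725 / (1 − 0.5) = 1450, against 1444 stated. Both reproduce.

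**Step 2. Chance of an aligned draw.** Two of the 2³ = 8 allocations give the intervention to the same type everywhere: 2/8 = 25%.

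**Step 3. Power with hospital, ward type and period in the model.** Power = Φ(0.916/SE − 1.645).
- *Aligned draw.* The estimate is a difference in differences. Expected pADEs are 240 × 0.05 = 12 per type at baseline, 482 × 0.05 = 24.1 in control and 482 × 0.02 = 9.64 in intervention. Variance = 1/12 + 1/12 + 1/24.1 + 1/9.64 = 0.312; SE 0.559; power 49.8%.
- *Split draw (two of one type, one of the other).* Variance from the expected information matrix is 0.154; SE 0.392; power 75.5%.
- Simulation of the regression gives 48% and 78%.
- Average over all draws: 0.25 × 49.8 + 0.75 × 75.5 = 69%.

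The R² of treatment on these covariates, weighted by admissions, is 0.75 in an aligned draw and 0.31 in a split draw (0.60 and 0.19 if weighted by expected pADEs). If the article's 50% allowance is read as this R², which is the reading that reproduces 1444, an aligned draw exceeds it and a split draw does not.

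**Step 4. Dependence on the model.**

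| Terms besides treatment | Aligned | Split |
|---|---|---|
| hospital, period | 78% | 78% |
| hospital, type, period | 50% | 75% |
| ward, period | 50% | 50% |
| hospital, type, period, type × period | not estimable | 74% (variance 0.162) |
| ward, period, type × period | not estimable | 46% (variance 0.349) |

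**Step 5. Sensitivity of the second row.** With centre shares up to 60/25/15 and a pADE rate ratio between types of 1 to 2, power is 46–50% when aligned and 64–78% when split.

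**The case against.** The strongest objection is that both the layout and the model are assumed. The sentence on gastro-intestinal and vascular patients fits mixed wards as well as single-type wards, and a centre may have more than two wards. The covariates are given as examples, and the final model is normally left to the analysis plan. This stands: the 25% and the 50% v 75% are conditional figures.

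The second objection is that the stated purpose of the baseline phase points towards ward-specific adjustment. If that is done with ward-level terms, power is about 50% whatever the draw; the loss then comes from the baseline adjustment and not from alignment. This also stands. It limits the power argument but leaves the last two rows of the table untouched.

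Third, the article is condensed, and a restriction on the draw may exist in a fuller protocol. That is possible, so the point is that none is described, not that the draws are known to be independent.

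A reader might infer that the design ties treatment to ward type and so cuts power from 75% to 50%. The article does not support that. Under the assumed layout the loss arises in one draw in four. The tie is incomplete because the baseline phase separates the two, pooling 240 admissions and 12 expected pADEs per type. The 75% is a computed split-draw figure, whereas the article claims 80%. A reader might also expect confounding by type to bias the result directly, but that would require an unadjusted analysis, and the article plans adjustment.

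**Conclusion.** The point holds as a conditional, avoidable risk. If each centre has two equal wards of opposite type, an unrestricted draw has a 25% chance of alignment. Adjusting for hospital, type and period then gives about 50% power instead of about 75%. Excluding aligned draws would raise average power under that model from about 69% to about 75%. Without a type term, or with ward-level baseline terms, the draw makes no difference to power. In every model that allows time trends to differ by type, a split draw keeps the treatment effect estimable and an aligned draw does not. Because the calculations ignore between-ward variation, all the power figures are optimistic. This is an optional improvement; nothing the article states is wrong on this point.

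**What to change.** Add one sentence to the randomisation description in the Design section: where wards within centres differ in type, the centre allocations are drawn jointly, once, from those in which each ward type appears in both arms. State each ward's type alongside it.

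In the assumed layout this leaves 6 of 8 allocations, and each ward keeps a probability of 1/2 of being the intervention ward. It needs no extra patients, data or staff. If wards within centres do not differ in type, the restriction does not apply.

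The small downside is the reduced set of allocations. A randomisation-based test is not a useful companion to this change: its smallest one-sided p-value is 1/8 = 0.125 with 8 allocations and 1/6 = 0.167 with 6, so neither can reach 0.05.

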**Figure 1 F1:**
[figure not shown]
**SUREPILL study design and assessment**.

### Study population

Consecutive patients admitted to the surgical study wards for elective surgery with an expected length of stay of more than 48 hours will be included. Patients transferred from another hospital or from another ward within the hospital are excluded. Cross-over between the study wards will exclude the patient. Patients already included in the study will not be included for a second time in a following admission.

After evaluation by the Medical Ethics Committee (MEC) at the coordinating center (AMC Amsterdam) it has been decided that this study is exempt from ethical approval, because this study does not meet the criteria for Medical Scientific Research with humans under the Dutch Law (Dutch acronym: WMO). Informed consent was therefore not required. Furthermore, this protocol has been peer reviewed before study approval by the Dutch National Grant Committee of Health Care Efficiency Research (ZonMw grant 170882706).

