#### Ward-based pharmacy care

A clinical pharmacy team will perform the ward-based pharmacy interventions. This team consists of pharmacy practitioners (pharmacy technicians, who completed additional training for ward-based pharmacy interventions) and hospital pharmacists.

Patients admitted at an intervention ward will receive bedside care from the ward-based pharmacy team. These interventions are tailored to cover critical steps in the medication process during the surgical pathway. On admission the pharmacy practitioner will perform medication reconciliation in consultation with the patient. This includes verification of the current use of community pharmacy medication. During hospitalisation the hospital pharmacist will review the medication charts daily and will optimise drug therapy when needed. The pharmacist combines information from CPOE-alerts, laboratory results and medical record information, in liaison with the ward doctor (face-to-face communication). At discharge the pharmacy practitioner will review the medication prescriptions by comparing them with the medication at admission. Unintended discrepancies will be discussed with the ward doctor. In addition, the pharmacy practitioner will perform patient counselling and send a complete list of discharge medication to the community pharmacy and general practitioner.

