### Study outcomes and data collection

The primary outcome parameter is the number of preventable ADEs per 100 admissions. Secondary outcome parameters are severity of preventable ADEs, number of patients with preventable ADEs per total number of admissions, direct (non-)medical costs and indirect non-medical costs, extra costs per prevented ADE, number and type of pharmacy interventions, length of hospital stay, complications registered in a national complication registration system for surgery, number of readmissions within three months after the initial admission (follow-up), quality of life during follow-up and number of non-institutionalized days during follow-up.

To assess the incidence and severity of preventable ADEs, we will systematically evaluate patient records and the hospital information system by use of a developed and validated Trigger Tool. This tool is based on previously literature on trigger tools, such as the trigger tool for measuring harm in ICU patients [22], the trigger tool for detection of AEs in surgical patients [23] and the widely used Global Trigger Tool of the Institute for Healthcare Improvement [24,25]. This list of items, or triggers, are clues to identify potential pADEs. Previous studies have shown that a trigger tool can efficiently and consistently be applied to detect and identify preventable ADEs [26,27]. If patient records are positive for potential pADE triggers, an independent expert panel, consisting of senior hospital pharmacists and consultant surgeons, will assess the presence or absence of the potential pADE individually, blinded for the hospital and ward the patient was admitted to. They will determine the presence or absence by use of a causality assessment tool for surgical patients based on tools such as the Naranjo probability score and the WHO-UMC [28,29].

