This study also has its limitations. First, data collection for ADEs using the trigger tool method for surgical patients is retrospective. Information bias can play a role in the detection of preventable ADEs. Therefore, even though the trigger tool method is a standardised detection method, it may well underestimate the number of preventable ADEs. Secondly, to perform a cost-effectiveness analysis from a societal perspective, patients need to complete questionnaires to include data on health status and out-of-hospital use of resources. Without the need of an informed consent procedure as is the case in this study, the level of patient participation becomes less predictable. Finally, the ward-based pharmacy intervention has been standardized for the study, but work floor implementation may differ somewhat between different clinical pharmacy teams. Besides, the work of the clinical pharmacy team is partly performed by pharmacy technicians. Nevertheless, in many - certainly European - countries this may be easier to implement.

Although two studies have shown that decentralized clinical pharmacy care in the ward can reduce preventable adverse drug events [16,17], this study will provide new information to measure cost-effectiveness of clinical pharmacy care as well as a standardized strategy to intervene by a clinical pharmacy team. Searching for ways to improve patient safety in general and medication safety in particular remains focus of attention worldwide.

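### Intervention-phase patients are identified after open ward allocation through a judged 48-hour criterion; a later change in case mix is possible, and the baseline phase cannot remove it

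*Protocol article*

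**What the plan says.** - **Eligibility** (Study population): inclusion is consecutive, and the criterion is that patients having "elective surgery with an expected length of stay of more than 48 hours will be included". Informed consent was not required. Patients transferred in from elsewhere are excluded, as are those who move between study wards.
- **Timing of allocation** (Design): after the baseline phase, "in each centre, one ward will be randomly assigned (one-time randomisation) as intervention ward". The 964 intervention-phase admissions are therefore identified once the allocation is fixed.
- **Arm** (Ward-based pharmacy care): "Patients admitted at an intervention ward will receive bedside care from the ward-based pharmacy team". The arm follows from the ward of admission.
- **Visibility** (same section): the pharmacist works "in liaison with the ward doctor (face-to-face communication"), so ward staff know which ward has the intervention.
- **Blinding** (Study outcomes and data collection): the expert panel is "blinded for the hospital and ward the patient was admitted to". This covers outcome assessment, not inclusion or ward placement.
- **Role of the baseline phase** (Discussion): "By adding a baseline assessment it is possible to adjust for a priori differences between wards". The next sentence concludes that the effect of ward-based pharmacy care alone is thereby made clear.
- **Adjustment** (Sample size and data analysis): the Poisson regression names, as examples, site, ward type, observation period, baseline ADE level and patient age.

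**The concern.** When wards are randomised first and patients identified later, randomisation protects the comparison only if inclusion and placement do not depend on the allocation. Two steps here could depend on it: the judgement that a stay will exceed 48 hours, and the ward to which the patient is admitted. If either is applied differently on the two wards after randomisation, the arms differ in who is counted. That would carry into the primary pADE rate, and into length of stay and costs.

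The article relies on the baseline phase to deal with ward differences, and the Discussion also uses it to argue that a cross-over design may not be needed. A baseline rate describes a ward before randomisation. It carries no information on a change in inclusion that begins afterwards.

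**Working it through.** **1. The plan's own figure.** Inputs from Sample size and data analysis: 5 versus 2 pADEs per 100, one-sided 0.05, 80% power, equal arms. For a difference of two Poisson rates:

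n per arm = (1.645 + 0.842)² × (0.05 + 0.02) / 0.03² = 481, or 962 in total, against 964 stated.

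With 482 per arm, power = Φ(0.03/√(0.07/482) − 1.645) = 80.1%. The sample size is reproduced and is not in question here.

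**2. What the baseline adjustment removes.** Let λ be the control-ward rate, k the pre-existing ratio between the two wards, θ the true rate ratio, and m the factor by which a change in case mix after randomisation alters the intervention-ward rate.

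- Baseline: intervention ward λk, control ward λ. Ratio k.
- Intervention phase: intervention ward λkθm, control ward λ. Ratio kθm.
- Baseline-adjusted ratio: kθm / k = θm.

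The pre-existing difference k cancels; m does not. This holds whatever the size of the baseline sample.

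**3. How large m might be.** The documents give no value for m. All case-mix inputs below are assumptions. The test is a crude comparison of two independent Poisson rates with 482 per arm, and the whole change falls in one arm.

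*Extra low-risk inclusions, no true effect (θ = 1).* Let a share f of intervention-ward inclusions have r pADEs per 100, against 5 otherwise: m = [(1 − f) × 5 + f × r] / 5.

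| f | r | m |
|---|---|---|
| 0.10 | 2 | 4.70/5 = 0.94 |
| 0.15 | 1 | 4.40/5 = 0.88 |
| 0.20 | 0.5 | 4.10/5 = 0.82 |

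At m = 0.88 the one-sided rejection rate is Φ(0.006/√(0.094/482) − 1.645) = 11.2% instead of 5%.

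*Extra high-risk inclusions, true ratio 0.40.* The same formula gives:

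- f = 0.10, r = 10: m = 5.50/5 = 1.10; observed ratio 0.44; power Φ(0.028/√(0.072/482) − 1.645) = 74.1%.
- f = 0.15, r = 12: m = 6.05/5 = 1.21; observed ratio 0.484; power Φ(0.0258/√(0.0742/482) − 1.645) = 66.8%.

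*A second model as a cross-check.* Take a 50:50 mix of high- and low-risk patients with risk ratio R between them, and a shift of s in the mix: m = 1 ± 2s(R − 1)/(R + 1). For R = 2 to 4 and s = 0.05 to 0.20, m runs from 0.97 down to 0.76, or from 1.03 up to 1.24. A true 0.40 would appear as about 0.30 to 0.50.

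**The case against.** The case against has real weight.

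- **Safeguards.** Inclusion is consecutive, there is no consent step, only elective patients enter, and transfers are excluded. This removes a common route of differential recruitment in cluster trials and leaves discretion only over borderline stays and initial placement. That stands. It narrows the room for selection without closing it, because consecutive inclusion operates only after the stay has been judged and the ward chosen.
- **Full protocol not shown.** Who judges the expected stay, and how beds are booked, may be set out there. The absence of that detail from an article is not held against the plan. It would not support the Discussion's inference, which rests on the baseline data alone.
- **Adjustment.** The covariate list is open and includes age, so part of a case-mix change could be adjusted for. That is correct, but the adjustment would come from patient-level covariates, not from the baseline phase.

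Three stronger readings are tempting and are not supported:

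- A reader might infer that expected stay will be read back from actual stay, so that a pADE could itself make a patient eligible. The Discussion says only that "data collection for ADEs using the trigger tool method for surgical patients is retrospective"; that concerns event detection. The eligibility text says expected stay, and nothing places that judgement after discharge.
- A reader might infer that patients with many medicines will be steered to the ward with the pharmacists. No section says that beds are assigned or redirected in that way.
- A reader might infer that the arms will in fact be unbalanced, or that the intervention will be favoured. Neither can be derived from the article.

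**Conclusion.** The point holds as a risk, not as a demonstrated bias. Intervention-phase patients are identified after an open allocation, through a judged criterion and through ward of admission, so a differential change in case mix is possible. Its size and direction are unknown. The pre-randomisation rates cannot remove it, and this follows from the structure of the adjustment without any assumed number. The claim that the baseline phase isolates the intervention's effect therefore goes too far.

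The rate ratios of 0.82–0.94 and 0.44–0.48, the 11.2% rejection rate and the power of 67–74% are illustrations on assumed inputs and a crude test. They show that moderate shifts would matter and do not predict what will happen. The change is worth making because it costs little.

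**What to change.** 1. Judge the 48-hour criterion from information recorded at scheduling, before ward placement: either the booked stay, or a planned procedure on a list drawn up from pre-randomisation hospital data. Apply it identically to all wards in both phases.
2. Add planned procedure group to the primary Poisson model. Add number of home medicines only if it comes from a source recorded the same way in both arms, such as community pharmacy data at admission. Bedside reconciliation takes place only on the intervention ward, so a count taken from it could differ by arm for that reason alone.
3. Compare case mix by ward and period, so that a change after randomisation can be seen.
4. Reword the Discussion to say that baseline data adjust for pre-existing ward differences only.

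Cost: an amended eligibility sentence, a procedure list from existing hospital data, one or two extra covariates, a descriptive table and a reworded sentence. A few listed patients will turn out to have short stays, which slightly dilutes the event rate.
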